### Statistical methods

Full details of all planned statistical analyses will be included in a written statistical analysis plan (SAP), which will be completed before the final study database is locked for analysis. The SAP will specify those endpoints and will employ conventional frequentist methods (i.e., statistical significance tests). All final reports and publications will clearly identify and differentiate between pre-planned and post-hoc tests of statistical significance. When appropriate, value of p thresholds will be adjusted to compensate for increases in family-wise error rates associated with multiple testing. We will apply an ANCOVA, a linear model for MMSE at 18 months, depending on treatment adjusted for MMSE at baseline with a random intercept for randomisation stratification and block.

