### Design

This is a multicentre, phase IIa, double blinded, randomised and placebo-controlled clinical trial, using a parallel arm design for 18 months’ follow up. The allocation ratio is 1:1 (treatment:placebo). The participants will undergo detailed clinical assessments at the screening visit, baseline visit (day 1) and at weeks 4, 8, 24, 36, and 52 of the treatment phase. We will perform four phone controls in the escalation phase and at week 5, 12, 16, 20, 28, 32, 40, 44, and 48. Between screening visit and baseline (max. 90 days), we will perform mandatory lumbar punctures, MRI, DaTSCAN, ECG, rsEEG, blood analysis, clinical and cognitive assessments.

Each participant will receive five intra-participant dose escalations at 60 mg three times a day (TID) (days 1–7), 120 mg TID (days 8–14), 315 mg twice a day (BID) (days 15–28), 315 mg TID (days 22–28) and 420 mg TID (days 29–550) with ABX or placebo for the duration of 18 months. After this period, we will offer the treatment with ABX in an open-label extension phase for 12 months for all participants who will continue.

The study is carried out in seven Norwegian centres: Helse Fonna, Haugesund Hospital as the study-coordinating center and Haraldsplass Deaconess Hospital (Bergen), Stavanger University Hospital, Akershus University Hospital (Oslo), Oslo University Hospital, St. Olav Hospital (Trondheim) and the University Hospital of North Norway (Tromsø) are allocated study sites. The inclusion period began in May 2021.

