### Participants

Participants must fulfil the following inclusion criteria: a) diagnosis of possible or probable DLB or MCI-DLB according to the established McKeith criteria from 2017 and 2020, respectively (McKeith et al., 2017; IG et al., 2020), b) are in age range between 50 and 85 years, c) have MMSE score > 15 at screening, d) are on stable doses of antiparkinsonian or dementia or psychiatric medications at least 1 month prior to the study initiation, e) participant or participant’s caregiver are able to give informed consent to actual and further assessments and procedures and f) have a responsible caregiver >18 years old who has contact with the participant at least three times a week.

The main exclusion criteria are a) any clinically significant or unstable psychiatric, medical or surgical condition, b) major cardiovascular or cerebral event that occurred within 6 months prior to the first visit, c) advanced malign disease or other terminal illness, d) relevant medication, alcohol or drug abuse, e) known sensibility to or contraindication for ABX, f) female participants who are pregnant or currently breastfeeding, and g) not able to proceed with the study regime (i.e., like traveling to study site or dysphagia, or unable to perform supplementary examination because of contraindications, claustrophobia, etc.). For other detailed inclusion and exclusion, criteria see Table 2.

**Table 2 tab2:** Inclusion and exclusion criteria in the ANeED study.

Inclusion criteria	1. Age ≥ 50 and ≤ 85 years of age, both gender
	2. Confirmed diagnosis of DLB including mild cognitive impairment in DLB (DLB-MCI).
	3. MMSE score >=15 at screening
	4. Able and willing to provide informed consent prior to any study related assessments and procedures
	5. Capable of complying with all study procedures
	6. Willing to provide blood samples for genetic analyses of APOE and GBA
	7. Willing and able to self-administer or administer by a caregiver oral ambroxol medication, from day 1 to study end (at 60 mg TID (day 1-7), 120 mg TID (day 8- 14), 315 mg BID (day 15-21), 315 mg TID (day 22-28) and 420 mg TID (day 29-550)).
	8. Contact with caregiver at least 3 times a week, to ensure sufficient information from the caregiver regarding participant’s status and possible change in condition
	9. Able to travel to the participating study site

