### Randomisation and blinding

We will perform randomisation using the electronic case report form (eCRF) system (Viedoc^1^). The participants will be randomly assigned into two arms: ABX 1260 mg/d (in three doses per day) and placebo – in an allocation ratio of 1:1. Before randomisation, the participants will be stratified due to risk factors (number of APOEε4 alleles (0, 1, 2) and beta-amyloid in CSF: normal and low). Therefore, we will use a restricted randomisation method with blocking and stratification. The number of strata is six. The block size is 4 (McKeith et al., 2017) with number and blocks 6 (Webb et al., 2003). The independent data manager will provide randomisation, and the drug manufacturer will get the list and deliver drug kits numbered based on the stratification.

The patients, patient’s caregivers, all study personnel, monitors and statisticians are blinded until the end of the study, with the exception of an emergency unblinding procedure. The ABX and placebo are produced in a tablet form and identical in appearance and taste to blinding purposes. Placebo tablets with microcrystalline cellulose as the main compound will include denatonium benzoate as a residual amount of bitter substance as ABX tablets have. Each participant will get the investigation medical product (IMP) in sequentially numbered identical containers according to the randomisation schedule. The responsible pharmaceutical company, Kragerø Tablettproduksjon AS, will send IMP shipments directly to each participating centre for dispensing and storage for the study.

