### Sample size

The primary outcome in this study is the mean score between the two groups (placebo and ABX) at 18 months. Both groups included patients with prodromal DLB and DLB. Based on our published data from the Dementia Study of Western Norway, where we included persons living with mild DLB (MMSE 23 points average at baseline) with annual follow-up, we found that the annual decline during the first 2 years of follow-up is 2 points for DLB with a standard deviation of 5.7. Based on these data, we estimated a 3-point decline at 18 months. We applied a sample power analysis to calculate the number of participants needed to detect a 3-point difference in the MMSE-NR3 scores at 18 months for 80% power to find a difference between the active treatment group and the placebo group and accounted for 25% drop-out. Based on these data, we estimated the sufficient number of participants to be 180.

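### The primary ANCOVA has no term for entry diagnosis (MCI-DLB or DLB) or centre, although both are known at baseline: a small, cheap gain in precision is missed

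*Protocol article*

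**What the plan says.** The Statistical methods section defers full detail to a SAP, to be completed before database lock, but still commits to a primary model in words. That model is a linear model for MMSE at 18 months on treatment, "adjusted for MMSE at baseline with a random intercept for randomisation stratification and block".

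The section on randomisation and blinding gives the stratification factors as "number of APOEε4 alleles (0, 1, 2) and beta-amyloid in CSF: normal and low". It adds that "The number of strata is six" and "The block size is 4", with allocation "in an allocation ratio of 1:1". Three APOE levels times two amyloid levels already make up the six strata, so neither stage nor centre is among them.

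Both omitted variables are fixed at entry. The first inclusion criterion in the Participants section requires a "diagnosis of possible or probable DLB or MCI-DLB according to the established McKeith criteria". The Sample size section states that "Both groups included patients with prodromal DLB and DLB". The Design section states that "The study is carried out in seven Norwegian centres".

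**The concern.** The article's Background names heterogeneity of symptoms and disease course as a difficulty for DLB trials, and argues for including prodromal patients because treatment should start early. On that reasoning, stage at entry is a plausible predictor of MMSE at 18 months. Baseline MMSE carries some of this information but perhaps not all: a prodromal patient and a patient with dementia can have the same score and then decline at different rates. Centre is a second possible source of variation, because seven sites administer the MMSE.

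The model does include a block term. No stratification by centre is described, so block mainly reflects order of recruitment within a stratum and does not stand in for site.

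At stake are some unexplained variance in the primary comparison and a question of credibility. If the arms happen to differ in stage, readers will ask for a stage-adjusted result. Under the article's own rule separating pre-planned from post-hoc tests, such an analysis added later would count as post hoc.

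**Working it through.** **Inputs from the article (Sample size section):** target difference 3 points; SD 5.7, attached there to the decline in a mild DLB cohort; power 80%; drop-out 25%; total 180. Alpha is not stated and is taken here as 0.05 two-sided.

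**Assumptions not in the article:** MCI-DLB share p = 0.2 to 0.5; stage difference D = 1 to 3 points in 18-month MMSE at a given baseline MMSE; centre intraclass correlation (ICC) 0.01 to 0.05; 5.7 used as the residual SD of the stated model.

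**Step 1, the plan's own figure.** n per arm = 2 × (1.96 + 0.842)² × 5.7² / 3² ≈ 56.7, so 57, or 114 in total. Dividing by 0.75 gives 152 (155 with the exact t-test). The stated 180 does not follow from these inputs. That is a separate matter, but it explains why the power below starts above 80%.

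**Step 2, power without stage or centre.** Completers = 180 × 0.75 = 135. SE = 2 × 5.7 / √135 = 0.98. Power = Φ(3/0.981 − 1.96) = 86.4%.

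**Step 3, adding stage.** Residual variance = 5.7² − p(1 − p)D². The chance difference in MCI-DLB share between arms has SD √(4p(1 − p)/135), so its 95% limit is 1.96 × 0.069 = 0.135 at p = 0.2 and 1.96 × 0.086 = 0.169 at p = 0.5. Multiplying by D gives the shift in the estimate at that limit.

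| D (points) | Residual SD, p = 0.2 to 0.5 | Power with stage | Shift at 95%-limit imbalance (points) |
|---|---|---|---|
| 1 | 5.69 to 5.68 | 86.5-86.6% | 0.13-0.17 |
| 2 | 5.64 to 5.61 | 87.0-87.4% | 0.27-0.34 |
| 3 | 5.57 to 5.50 | 87.9-88.7% | 0.40-0.51 |

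Stage explains between 0.16/32.49 = 0.5% and 2.25/32.49 = 6.9% of the residual variance. The number needed for 80% power falls from 152 to between 152 and 142. The largest shift, 0.51, is about half of the 0.98 standard error.

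**Step 4, adding centre.** Residual SD = 5.7 × √(1 − ICC): 5.67 at 0.01 and 5.56 at 0.05. Power is 86.7% to 88.0%.

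**Step 5, could the strata carry these factors?** With stage there would be 12 cells of 180/12 = 15 patients. With centre there would be 42 cells of about 4.3, and with both 84 cells of about 2.1, using blocks of 4. Stratifying on centre is therefore not workable at this size; covariate adjustment is.

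**The case against.** The strongest objection is that nothing here is invalid. ANCOVA on baseline MMSE with terms for the randomisation strata is a sound analysis that reflects the design, and the SAP, which is not shown, may add covariates. The first part stands. The second stands only in part: the article does not merely leave the model open but writes one out, so settling its terms now is a concrete change to stated text.

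A reader might go further and infer that stage imbalance biases the treatment comparison or inflates the type I error. The documents do not support that. Under 1:1 randomisation an imbalance in stage can arise only by chance, and its contribution is already part of the standard error. The shifts tabulated above are conditional on an unlucky allocation and do not describe a systematic error.

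A reader might also fault the stratification for leaving out stage and centre. That is not supported either. The Discussion gives a prognostic reason for the factors chosen, namely AD co-pathology, and adding centre would leave cells too small for blocks of 4.

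Two further points limit the size. A 3-point stage difference equals the whole 18-month decline that the Sample size section expects in DLB, so the top of the range implies almost no decline in MCI-DLB. And no site or rater difference is documented; the article plans frequent cross-site meetings for consistency, so the centre ICC is purely an assumption.

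**Conclusion.** The point holds as a modest missed gain in precision. Entry diagnosis and centre are known for every participant and are absent from the primary model as written. Under the assumptions listed, stage adds about 0.1 to 2.3 percentage points of power to a baseline of 86.4%, and centre about 0.3 to 1.6. If D is near 1, the gain from stage is negligible. At a 95%-limit imbalance the estimate would move by about 0.13 to 0.5 points against a 3-point target, the upper end being an extreme case.

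All of this depends on the MCI-DLB share, the stage effect left after baseline MMSE, and the centre ICC, none of which the article gives. It also depends on using 5.7 as the residual SD. If baseline MMSE explains more, for example with an assumed correlation of 0.6 and a residual SD of 5.7 × √(1 − 0.36) = 4.56, power is already about 97% and the possible gain is smaller still. The case for acting is that the change costs almost nothing and counts as pre-planned only if made in advance.

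**What to change.** Before unblinding, and in the SAP at the latest, add to the primary MMSE model:

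- entry diagnosis (MCI-DLB or DLB) as a fixed covariate;
- centre as a random intercept.

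Keep baseline MMSE and the stratification factors, and leave the randomisation unchanged. Use the same added terms for the continuous secondary outcomes. Do not extend them to sparse count or event outcomes such as withdrawals, dose reductions and adverse events, where a stage term plus a seven-centre random effect may be unstable.

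The cost is a change of wording, one degree of freedom for stage and one variance component for centre. No new data are needed.

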### Data handling and storage

The data will be handled in accordance with the European Union (EU) General Data Protection Regulation and in accordance to the GCP. The eCRFs will not bear the participants’ names or other personal identifiable data. The participants’ trial identification numbers will be used for identification and this will be clearly explained to the participants on the patient’s information sheet.

All study sites have access to the digital eCRF platform Viedoc (see text footnote 1). This platform is assigned to manage health and research data and has been approved for drug trials in the EU/European Economic Area including Norway. Each participant receives a personal identification number to ensure that the data are anonymised. Additionally, all CRFs are stored in paper forms and are safely archived. All other data in electronic forms (EEG, MRI and DaTSCAN) are archived in local, secure servers held by the Information and Communication Technologies service in Norway.

All study personnel are trained to comply with GCP regulations, protocols, and all standard operating procedures (SOPs). Additionally, all CRFs are stored in paper forms and are safely archived.

Archiving will be authorised by the sponsor following submission of the end of the study report in collaboration with Viedoc. The CI is responsible for the secure archiving of essential trial documents and the trial database as per their trust policy. All essential documents will be archived for a minimum of 15 years after completion of the trial and in adherence to the Norwegian Medicine Agency’s (Statens Legemiddelverk) recommendations.

Frequent meetings will be held between and across the study sites in order to ensure quality and consistency. The data will be frequently monitored on site, and including but not limited to source data verification, inclusion and exclusion criteria (serious), AEs protocol deviations and IMP drug data.

## Discussion

Here, we present here our protocol for the ANeED study testing ABX in prodromal and mild DLB. Prodromal stages of DLB are now defined for research purposes and these individuals, including those with mild dementia and those who need to be offered inclusion in clinical trials to establish treatment options with disease modifying drugs in DLB.

The rationale for the use of ABX in DLB is firmly established and is based on both preclinical and clinical data. Because GCase activity is associated with aS metabolism, enhancing CMA may potentially reduce pathological aS depositions. Preclinical trials of ABX in models of synucleinopathies are promising and showing the effects of reducing the concentration of toxic aS species. ABX penetrate into CSF (Mullin et al., 2020) and first trials have shown an enhancing effect of ABX on GCase activity in human cells.

Our study is the largest ongoing clinical trial with ABX and the first in patients with prodromal and mild DLB. To date, we have included 47 patients in the study and 30 who started medication in the first 12 months; we observed good tolerability with only a few side effects. There are also seven candidates waiting for a screening visit.

One previous study on ABX in PD was carried out in only 17 participants, and it was not randomised or placebo controlled (Mullin et al., 2020); another is now completed with 50 patients with PDD (Silveira et al., 2019). The goal in our study is to recruit 180 participants, a number sufficient to find a difference between the active treatment group and the placebo group at 18 months based on the MMSE. However, 180 participants might not be enough to apply for a marketing authorisation if the study turns out to show the effect of ABX on DLB.

Based on our previous research, we know that the combined significant AD pathology in DLB will worsen prognosis; therefore, we decided to stratify the participants in our study based on APOEε4 genotypes and CSF Aβ_1-42_ to secure equal groups for placebo and ABX. We will also extend the study duration to 18 months and thereafter to 12 months of open extension to maximise the chances of showing treatment effects.

In this study, we will include an extensive biomarker program including MRI, rsEEG, genetics and a broad spectrum of digital bio-markers. We will also implement the extremely promising CSF Real-Time Quaking-Induced Conversion method for assessing aS-pathology in CSF. This method has a reported sensitivity above 95%, with a specificity of 98% for DLB and other synucleinopathies (Rossi et al., 2020). We hope that our study will bring more knowledge about ABX’s safety, tolerability and efficacy in the drug treatment of synucleinopathies, such as DLB. We also hope that treatment will show effects on both clinical outcome measures, and digital and traditional CSF biomarkers.

### Ethics

The study protocol and all informed consent forms were approved by the Regional Ethics Committee (REK 73910) and other regulatory organs, such as the Norwegian Medicine Agency and Norwegian Centre for Research Data (NSD; 582,472), prior to any participants’ recruitment. The trial is registered in the international trials register - www.clinicaltrials.gov (NCT0458825) and nationally at the Current Research Information System in Norway (CRISTIN 2235504). It is also the responsibility of the CI, PI or designee at each site to ensure that all subsequent amendments gain the necessary approvals, including approval from data protection official at the site. This does not affect the individual clinician’s responsibility to take the immediate action necessary to protect the health and interests of individual participants for reporting urgent safety measures.

All participants, or – if participant due to the mental disability, a participant will not be able to give consent – caregivers, will be informed about the study, study procedures and medication and will have the right to discuss all doubts and questions before enrolment. The participants will be free to refuse to participate in any study phase and for any reason. They will be asked whether they wish to be told the results of their genotyping and counselled accordingly as part of standard of care procedures by the local PI or study clinician.

## Ethics statement

The studies involving human participants were reviewed and approved by Regional Ethics Committee, REK 73910. The patients/participants provided their written informed consent to participate in this study.

